**Figure 1 F1:**
[figure not shown]
**Overview of study activities**.

#### Screening

The 10-item Alcohol Disorder Identification Test (AUDIT) [24] assesses alcohol consumption level (3 items), symptoms of alcohol dependence (3 items), and problems associated with alcohol use (4 items). Responses to items on the AUDIT are rated on a 4-point Likert scale from 0 to 4, for a maximum score of 40 points. Higher AUDIT scores indicate more severe levels of risk: a score of 8 indicates a tendency for problematic drinking. To comply with the timeline of this study, all subjects were asked for their alcohol consumption in the previous 3 months rather than in the past 12 months.

The primary outcome measure used in this study is the change in drinks per week from baseline to follow-up, as estimated from the first two AUDIT questions. A secondary measure is the frequency of consuming four or more drinks per occasion (AUDIT question 3). We will also evaluate the percentage of patients whose weekly consumption decreases, increases, or remains the same, as well as changes in a combination of the first three AUDIT item scores called the Drinkers' index, in order to estimate the amount of alcohol risk reduction.

#### Consent

Consent to participate will be obtained in a 2-stage process. Research assistants will initially ask for informed consent to conduct a health screen and collect basic information and check eligibility to take part. No identifiable information will be collected at this stage. Patients who have a positive score on the AUDIT (alcohol risk score), as applicable, will have the study explained to them verbally and in writing (using the patient information sheet). Informed consent will be obtained at this second stage which will include permission to give the contact details to the research staff, and participate in the experimental or control condition and follow up after 3 and 6 months by the research assistant.

#### Interventions

##### Health Education Leaflet

All the patients randomized and allocated to the control group will complete the baseline measures and will receive a health education leaflet on responsible drinking.

##### Brief Counselling

The patients randomized and allocated to the intervention arm will complete baseline measures and receive brief counselling for alcohol reduction intervention. The goals for brief counselling are as follows: 1) To identify any alcohol- related problems mentioned in the interview, 2) To introduce the sensible drinking leaflet, emphasis the idea of sensible limits, and make sure that patients realize that they are in the risk drinking category, 3) To provide feedback on the relationship between alcohol and TB treatment [25,26], 4) To work through the first 3 sections of the problem solving manual while mentioning the value of reviewing the other sections, 5) To describe drinking diary cards, 6) To identify a helper, and 7) To plan a follow-up counselling session.

The Information-Motivation-Behavioural Skills (IMB) Model will be used in the study to guide the alcohol reduction intervention. The IMB model [27-29] proposes that *information *about alcohol misuse and methods of reducing and preventing harmful and/or hazardous drinking is a necessary precursor to risk reduction. *Motivation *to change, however, also directly affects whether one acts on information about risk and risk reduction. Finally, the IMB model holds that *behavioural skills *related to preventive actions represent a final common pathway for information and motivation to result in alcohol risk behaviour change. The IMB model posits that information and motivation activate behavioural skills to ultimately enact risk reduction behaviours. The IMB model also shows that information or motivation alone can have direct effects on some preventive behaviour, such as when information about risky alcohol drinking prompts drinking in moderate levels or to stop drinking.

However, behavioural skills become increasingly important when preventive actions require complex skills such as requesting that a family member, friend, or patient to reduce amount of alcohol, avoiding alcohol use in sexual contexts, or to stop drinking. Thus risk reduction skills are theorized to have a direct effect on risk reduction behaviours, and information and motivational enhancement may have direct effects as well as indirect effects on risk reduction behaviours. The content of brief interventions has varied somewhat in research and demonstration projects. Most programmes are instructional and motivational, designed to address the specific behaviour of drinking with information feedback, health education, skill-building and practical advice, rather than with psychotherapy or other specialized treatment techniques [24].

##### Assess and Tailor Advice to Stage of Change

Further assessment beyond initial screening can be an important aid to brief counselling. Diagnostic assessment involves a broad analysis of the factors contributing to and maintaining a patient's excessive drinking, the severity of the problem, and the consequences associated with it. Another type of assessment is the motivational stage of the patient, which can vary from no interest in changing drinking behaviour (pre-contemplation) to actual initiation of a drinking moderation plan (action stage). The Stages of Change represent a process that describes how people think about, initiate, and maintain a new pattern of health behaviour. The five stages are each matched with a specific Brief Intervention element. One of the simplest ways to assess a patient's readiness to change their drinking is to use the "Readiness Ruler" recommended by Miller. Ask the patient to rate on a scale of 1 to 10, "How important is it for you to change your drinking?" (with "1" being not important and "10" being very important). Patients who score in the lower end of the scale are pre-contemplators. Those who score in the middle range (4-6) are contemplators, and those scoring in the higher range should be considered ready to take action. It is helpful to begin counselling in a way that meets the patient's current motivation level. For example, if the patient is at the pre-contemplation stage, then the advice session should focus more on feedback in order to motivate the patient to take action. If the patient has been thinking about taking action (contemplation stage), emphasis should be placed on the benefits of doing so, the risks of delaying, and how to take the first steps. If the patient is already prepared for taking action, then the health worker should focus more on setting goals and securing a commitment from the patient to cut down on alcohol consumption. For most patients, the standard sequence of Feedback, Information, Goal Selection, Advice, and Encouragement should be followed, with minor modifications dictated by the current stage of change.

##### Using the tuberculosis illness episode to engage the patient

The content of the brief counselling intervention includes normative feedback on the patient's alcohol consumption, including encouraging the patient to reflect on how drinking may be impacting his or her health. Incorporating feedback on the relationship between alcohol and TB treatment is an important component of the intervention. Counsellors provide general information on the negative consequences of alcohol misuse on TB treatment outcomes and TB treatment adherence, exploring the association between drinking and the risk of unsuccessful TB treatment [25].

##### Provide Skills Training via the Self-Help Bookle

After assessing the patient's readiness to change drinking behaviour, the provision of a self-help booklet is recommended. A modified version of the self-help manual used in the WHO Project on Identification and Management of Alcohol-Related Problems as adapted to South Africa has been developed by [30].

### Counsellor training and intervention quality assurance

The intervention counsellors will consist of existing lay counsellors and nurses from the study clinics speaking the predominant languages in the area (English, Afrikaans, Zulu, Xhosa and Tswana) and they will deliver the interventions to men and women as per usual clinic services. All lay counsellors and up to four nurses per study clinic who are suitable to deliver the brief counselling intervention will receive formal training (lay counsellors 3 days and nurses 2 days) and supervision. The training takes a practical, systems approach, aiming to facilitate the implementation of SBI in clinic operations rather than merely educating staff. The training curriculum contains modules addressing practical issues deemed essential to implementing the programme. For early identification of alcohol problems in primary care the Alcohol Use Disorders Identification Test (AUDIT) [24] and for the brief intervention the WHO brief intervention package for hazardous and harmful drinking [24] will be used. Both were adapted to the South African context, e.g. in terms of standard unit of alcoholic drink and drinking limits. The AUDIT was translated and back translated according to scientific standard procedures [31] into four of the major languages (Tsonga, Northern Sotho, Venda, and Afrikaans) [13] and will be translated into additional languages (Xhosa, Zulu and Tswana). The self-help booklet for patients and a handout on "cutting back" showing the drinking limits and health effects of risky alcohol consumption were also made available in the target languages. The AUDIT manual explains the purpose of screening for alcohol problems in primary care, the context of alcohol screening, the development and validation of the AUDIT, administration guidelines, scoring and interpretation. The Brief Intervention manual defines concepts and terms, roles and responsibilities of Primary Health Care, SBI: a risk management and case finding approach, alcohol education for low-risk drinkers, abstainers and others, and simple advice an brief counselling for risk zone drinkers, self-help booklet and training sources. Critical administrative activities include administration and scoring of the screening instruments, assuring availability of patient brochures, sequencing of interventions with treatment of presenting health problems, the essential elements of an intervention, and the management of SBI records.

The training will comprise of four elements: orientation to the relevant practice, standardised PowerPoint presentation, tape recorded simulated consultations with trained actors and ongoing clinical supervision by experienced HSRC staff. The simulated consultations will be recorded and rated by two independent clinical assessors. The brief intervention counsellor will be assessed for adherence to the brief counselling protocol in addition to their behaviour and skills using a Behaviour Change Counselling Index. Assessors will submit the ratings, comments and supervision points for each consultation. This information will support clinical supervision and training until the brief intervention counsellor reaches a required standard of practice agreed by the assessors [32,33].

To help protect against counsellor drift, the brief intervention will be completely manualized and can be used to guide the counsellor through the session content. Site visits will be done bi-weekly by the project manager to offer support and supervision to the trained clinic based study fieldworkers. In terms of control around the quality and consistency of the implementation of the intervention, intervention counsellors will fill in a patient for each counselling session conducted. It includes sections on client's AUDIT score, stage of change, action and intervention plan, handing of action plan to client and comments. Intervention counsellors will be compensated with R20 (US$2.6) for each counselling session conducted and monitoring form completed. In addition, study fieldworkers will be able to report to their coordinators regarding any problems they may be having in implementing the brief interventions. Regular meetings between the researchers and the project managers will allow for any problems to be resolved timeously.

#### Outcome Measures

##### Patient measures

###### Baseline

All patients (i.e. those in the treatment and control arms) will complete baseline measures which will include a Demographic Questionnaire, medical file information (HIV status, body weight, TB treatment outcome), a health status measure, namely, the SF-12, the AUDIT to measure alcohol use/misuse, anti-tuberculosis medication adherence and two questions which ask about tobacco use.

###### Follow-up

The same measures as detailed above will be administered (at follow-up) to the intervention and control groups of patients at 3 months and again at 6 months after the baseline measures are obtained.

Broadly speaking then, the primary outcome measure of the study is: (1) change in the mean score on the AUDIT in the last 3 months and mean number of heavy drinking days in the last month of the study period compared with baseline, as measured by the AUDIT.

The secondary outcome measures of the study are: (1) anti-tuberculolisis treatment adherence and (2) successful TB response, classified by WHO as cured or treatment completed (versus treatment failure, defaulted, died or transferred out to another health facility [34].

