##### Patients with active TB

New tuberculosis treatment patients (i.e. those patients who have been initiated or have been on anti-TB treatment for less than one month), males and females, 18 years and above who visit the primary health care facility and who score 8 or more for men and 7 or more for women on the AUDIT questionnaire after screening will be included in this study. Some researchers found that brief interventions are effective even among excessive drinkers [21-23]. Therefore patients scoring high on the AUDIT are included in the study.

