#### Analysis approach

The primary outcome will be measured at three time points: baseline, three and at six months. If a patient drops out, is not present on the day of the interview or refuses to answer questions the primary outcome at the end point of the trial will be missing. Therefore, except for the baseline measurement, no post-randomization information will be available for these participants. The extent of the missing component was estimated to be 10% at six months. The single follow-up measurement and the extent of the expected dropout has to be considered for the statistical method that can be used to provide an unbiased estimate of the intervention effect under the principle of intention to treat. The method that can be used to take account of the stratified cluster trial design, the repeated binary nature of the primary and secondary outcome (Risky drinking, TB treatment adherence, TB treatment outcome) and the missing data at follow-up is a weighted generalized estimation equations (WGEE) approach [35]. The method utilizes inverse probability weighting to correct for the bias associated with missing data that is not missing completely at random (MCAR) and participants with complete data are weighted with the dropout probability of participants with the same characteristics at baseline. To determine the weights a logistic regression model will be constructed for the dropout indicator utilizing measurements on the primary outcome (at baseline) and other variables taken at baseline or post-randomization. For comparison and checking an unweighted analysis will also be done.

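### TB treatment outcome is a single end-of-treatment classification, but the protocol schedules it at baseline, 3 and 6 months and analyses it as a repeated binary outcome

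*Protocol article*

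**What the plan says.** Four places in the protocol article bear on this.

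- **Inclusion criteria, Patients with active TB.** Those enrolled are "those patients who have been initiated or have been on anti-TB treatment for less than one month".
- **Outcome Measures, Baseline.** The list includes "medical file information (HIV status, body weight, TB treatment outcome" as well as "the AUDIT to measure alcohol use/misuse, anti-tuberculosis medication adherence and two questions which ask about tobacco use".
- **Outcome Measures, Follow-up.** "The same measures as detailed above will be administered (at follow-up) to the intervention and control groups of patients at 3 months", with the timing given as "at 3 months and again at 6 months after the baseline measures are obtained". The second of the two secondary outcomes in this section is "successful TB response, classified by WHO as cured or treatment completed (versus treatment failure, defaulted, died or transferred out to another health facility".
- **Data analyses, Analysis approach.** Weighted generalized estimating equations are chosen partly because of "the repeated binary nature of the primary and secondary outcome (Risky drinking, TB treatment adherence, TB treatment outcome".

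The protocol does not state the length of the TB treatment course.

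**The concern.** The categories that define the TB outcome describe how a course of treatment ended. Each patient gets one of them, once. A patient just starting treatment has none, and a patient midway can only have one if treatment has already ended badly. The schedule and the model description treat this classification like the AUDIT, as something that can be read at every visit and followed over time.

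If an analyst follows the text, the TB outcome has a baseline time point with no values and, in all likelihood, a 3-month time point with no successes. No odds ratio between arms can be estimated at either. The text also leaves open what to do with patients whose treatment is still running at 6 months.

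The outcome matters to the trial's purpose. It is one of two named secondary outcomes, it falls under the third objective and the second study hypothesis, and the Discussion rests its policy argument on TB cure rates.

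**Working it through.** There is no planned figure to reproduce: the sample size is for the AUDIT score, and none is given for the TB outcome. The check is one of timing.

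**Inputs**
- Time on treatment at enrolment: 0 to under 1 month (Inclusion criteria).
- Visits: 0, 3 and 6 months after baseline (Follow-up).
- Course length: not stated, so taken as 4, 6, 8 or 9 months, without interruption. These are assumptions.

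**Formula.** Months on treatment at a visit = visit month + time on treatment at enrolment.

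| Visit | Months on treatment | End reached, 4-month course | 6-month course | 8- or 9-month course |
|---|---|---|---|---|
| Baseline | 0 to <1 | none | none | none |
| 3 months | 3 to <4 | none | none | none |
| 6 months | 6 to <7 | all | all | none |

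**Reading the table**
1. At baseline no patient can be classified, whichever course length is assumed.
2. At 3 months no patient can be cured or have completed, for any course of 4 months or more. Default, death, failure and transfer out can already be on file. Among classified patients the success proportion is therefore 0% in both arms, and an odds ratio of 0 against 0 is undefined.
3. At 6 months the full classification exists for uninterrupted patients if the course is 6 months or shorter. It exists for none of the successes if the course is 8 or 9 months. A patient still on treatment at this visit is neither in the success group nor in the group it is compared with.

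So the complete success/non-success classification is available at one of the three visits at most.

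**Adherence, by contrast.** Patients who have not stopped are on treatment at the 3-month visit, so adherence can be observed there, and again at 6 months over the period treated. At baseline it can be observed, over less than one month, for patients already on treatment. It is undefined only for those enrolled on the day treatment starts.

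**Room for a later reading.** Recruitment lasts 6 months (Randomisation) and the study 15 months (Project Timescales). If recruitment opens at the start of the study, the last patient can be looked up 15 − 6 = 9 months after baseline. That is 9 − 6 = 3 months after that patient's last visit, with 9 to <10 months since starting treatment. Any set-up time before recruitment shortens this one for one.

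**The case against.** The best defence is that the wording is loose but not binding. The sentence that fixes three time points, "The primary outcome will be measured at three time points: baseline, three and at six months", concerns the primary outcome only, and the same section goes on to speak of one follow-up measurement. The parenthesis listing three outcomes may serve only to justify one method, and weighted estimating equations can handle one observation per patient. The article is also condensed, so the date of the final file look-up and the handling of patients still on treatment could properly sit in a fuller document.

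Part of this stands. The method can be kept, and a missing look-up date alone would be no finding. But the protocol is not merely silent. It places TB treatment outcome in the baseline list, repeats that list at both follow-ups, and calls the outcome repeated. Those statements contradict its own definition of the outcome.

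Three stronger readings are tempting and should not be drawn.

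- *That neither secondary outcome can be analysed as repeated.* This is wrong for adherence, as shown above. The TB outcome itself remains analysable as a single endpoint.
- *That the effect will be diluted by a known amount.* Assume success of 75% against 80%: the odds ratio is (0.80/0.20)/(0.75/0.25) = 1.33. Adding a 3-month row scored as non-success gives 37.5% against 40%, odds ratio 1.11. A baseline row as well gives 25% against 26.7%, odds ratio 1.09. This needs a rule that scores patients still on treatment as unsuccessful. The protocol has no such rule, and its definition suggests they are simply unclassified. The rates are assumed too, so this is illustration only.
- *That those without a 6-month outcome are the patients who interrupted treatment.* This depends on an assumed 6-month course. With a longer course uninterrupted patients also lack an outcome, and some who interrupt may already be classified as defaulted. Any probability of still being on treatment would further need an assumed spread of enrolment days and day-for-day make-up of missed doses.

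**Conclusion.** The point holds for TB treatment outcome. A single final classification is scheduled as a measure repeated from baseline and described as repeated binary in the analysis. The baseline conclusion needs no assumption. The 3-month conclusion, that only unfavourable states can be recorded, needs a course of at least 4 months. How many patients are unclassified at 6 months cannot be worked out from the document.

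The consequence is confined to one secondary outcome. No size of bias can be given, because the protocol does not say how patients still on treatment would be coded. The Baseline, Follow-up and Analysis approach sections need to be brought into line with the outcome definition.

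**What to change.** - **Baseline and Follow-up:** remove TB treatment outcome from the baseline and 3-month measures. Define it as one binary endpoint per patient, read from the medical file when treatment closes. For patients still on treatment at the 6-month visit, make a final look-up before the 15-month study ends, and state how anyone still unclassified then will be handled.
- **Analysis approach:** take TB treatment outcome out of the repeated-binary description. Compare it once between arms, still allowing for clinic clustering, the stratification, and weighting for patients with no recorded outcome.
- **Adherence:** keep it as a repeated measure at 3 and 6 months. If a baseline value is collected, note that it does not exist for patients enrolled on the day treatment starts.

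The cost is a change of wording and one late file look-up. For some patients the outcome will be known later, by up to about 3 months for the last enrolled. Control patients are due the delayed counselling after their 6-month follow-up (Procedure). An outcome that closes after that point may therefore partly reflect it, and the report should say how many such patients there are.
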